## Abstract

**Background:**

Heart failure (HF) is characterized by an increasing prevalence, representing a public health problem and a significant cause of morbidity and mortality. Self-care is a cornerstone approach for optimizing therapy for patients with HF. Patients play a crucial role in managing their condition, given that several adverse health outcomes might be avoided with adequate self-care. In this regard, the literature describes motivational interviewing (MI) as highly favorable for treating chronic diseases, with promising results supporting its efficacy in enhancing self-care. Moreover, caregivers’ availability constitutes a fundamental supporting factor among the strategies to improve self-care behaviors in people with HF.

**Objective:**

The primary study aim is to test the efficacy of a structured program, including scheduled MI interventions, in improving self-care maintenance in the 3-month follow-up from the enrollment. Secondary aims comprehend the assessment of the effectiveness of the above intervention on secondary outcomes (eg, self-care monitoring, quality of life, sleep disturbance) and the corroboration of the superiority of caregivers’ participation to the intervention over the program administrated only to individual patients in enhancing self-care behaviors and other outcomes at 3, 6, 9, and 12 months from the enrollment.

**Methods:**

This study protocol designed a prospective, parallel-arm, open-label, 3-arm, controlled trial. The MI intervention will be administered by nurses trained in HF self-care and MI; the education program will be provided to nurses by an expert psychologist. Analyses will be performed within the framework of intention-to-treat analysis. Comparisons between groups will be based on an alpha of 5% and 2-tailed null hypotheses. In the case of missingness, analyzing the extent of the missingness and identifying underlying mechanisms and patterns will guide imputation methods.

**Results:**

The data collection was started in May 2017. We completed the data collection with the last follow-up in May 2021. We plan to perform data analysis by December 2022. We plan to publish the study results within March 2023.

**Conclusions:**

MI enhances potential self-care practices in patients with HF and their caregivers. Although MI is effectively largely employed either alone or combined with other treatments and is administered in different settings and ways, face-to-face interventions seem to be more effective. Dyads with higher shared HF knowledge are more efficient in promoting self-care adherence behaviors. Moreover, patients and caregivers may perceive proximity with health care professionals, resulting in a better ability to follow the received health professionals’ directions. The scheduled in-person meetings with patients and caregivers will be exploited to administer MI, respecting all the safety regulations for infection containment. The conduction of this study may support changes in clinical practice to include MI to improve self-care for patients with HF.

**Trial Registration:**

ClinicalTrials.gov NCT05595655; https://clinicaltrials.gov/ct2/show/NCT05595655

**International Registered Report Identifier (IRRID):**

DERR1-10.2196/44629

## Introduction

Heart failure (HF) is defined as “a clinical syndrome with symptoms and or signs caused by a structural and/or functional cardiac abnormality and corroborated by elevated natriuretic peptide levels and or objective evidence of pulmonary or systemic congestion” [1]. HF is characterized by an increasing prevalence and burden, representing a public health problem and a major cause of morbidity and mortality [1,2]. Globally, the overall estimated incidence of HF disease is 1-4 cases per 1000 person-years, with a prevalence of 10-30 cases per 1000 persons [3]. The incidence of the disease in Europe is about 5 per 1000 person-years, with a prevalence of 1%-2% in adults [4]. The prevalence of HF increases significantly with age: 6.6% of men with HF are aged 60 to 79 years, and 10.6% are aged 80 years and older [5].

Due to the impact of the disease, some authors have defined HF to be the “global outbreak” of the 21st century about 25 years ago [6,7]. An estimated 64.3 million people worldwide are affected by HF [7]; the growing and aging of the population, the high survival rate after an acute coronary event, and the effectiveness of secondary prevention and drug treatment result in a constant increase in the number of patients living with HF [4,7-9]. HF is most frequently diagnosed in patients who are hospitalized and 65 years and older [10]. People surviving at 1 and 5 years of follow-up have increased by about 20% compared to 1950-1970s [11]; however, 5-year mortality is still high, resulting in 24.4% for people aged 60 years and 54.4% for people aged 80 years [5].

Outcomes related to HF have improved in recent years [4]. Thus far, hospitalization and rehospitalization still impact the health care system; treating patients with HF costs US $30 billion every year, and this figure is destined to grow further, reaching US $70 billion by 2030 in the United States [5]. Once HF is first diagnosed, patients are readmitted to the hospital about once a year; this trend contributes to increasing health care resource consumption and worsens patients’ quality of life (QoL) [7,12]. Moreover, HF is associated with considerable morbidity and mortality [13]. A 60- to 90-day mortality from diagnosis is about 10% in patients with HF; 1-year mortality is about 36% [14].

Self-care is a cornerstone approach for optimizing therapy for patients with HF [15]. Self-care is defined as an active, cognitive process through which people engage to maintain their health (self-care maintenance) and recognize and manage signs and symptoms (self-care monitoring and management, respectively) [16]. Precisely, self-care maintenance is defined by behaviors to preserve physical and psychological status, self-care monitoring encompasses behaviors about the ability to recognize signs and symptoms, and self-care management consists of the ability to manage signs and symptoms when they occur [17,18]. The consequences of inappropriate self-care behaviors can be dramatic, resulting in emergency hospital admissions, recurrent hospitalizations, and preventable complications. Poor adherence to treatments and improper disease management are the main causes of the exacerbation of HF [19-21]. In this regard, patients play a key role in the management of their condition, given that several negative health outcomes might be avoided with effective self-care [20,22].

Caregivers’ availability constitutes a key supporting factor among the strategies to improve self-care behaviors in people with HF [23]. Studies involving patients with HF and their caregivers [24-26] report that self-care in HF is a “dyadic phenomenon” [27]: informal caregivers, such as a family member or a close friend, are fundamental in contributing to HF patients’ self-care, as they provide tangible and emotional support and cooperation [23]. Caregivers tend to adapt their conduct based on patients’ ability to care for themselves: they may act by reminding self-care behaviors or replacing the patient in the self-care process.

Many international studies have tested interventions to improve self-care in patients with HF involving caregivers to enhance the effectiveness of educational interventions [25,28,29]. Among the interventions reported in the literature, motivational interviewing (MI) has been described as highly favorable for treating chronic diseases, with promising results supporting its efficacy in enhancing self-care [30]. This intervention is a directive client-centered counseling approach for eliciting behavioral change by helping people to explore and resolve ambivalence. MI considers several critical factors in improving self-care in patients with HF and is based on brief interventions, which are feasible in several health care settings [30,31].

A recent study involving patients with HF and their caregivers tested the efficacy of MI in improving self-care maintenance, self-care management, and self-care confidence in adults with HF at the 3-month assessment after enrollment [32]. In this study, a 1-year follow-up was also performed, and the MI was performed only once. The influence exerted by caregivers on self-care behaviors employed by patients was also assessed using a 3-arm design [32]. More precisely, in the first arm, MI was administered to patients only; in arm 2, MI was administered to patients and caregivers; and in arm 3, participants received usual care (standard education). The study demonstrated that MI performed by trained nurses effectively improved self-care in patients with HF, especially in the arm where it was administered to both patients and caregivers [32]. However, the 1-year follow-up showed that the effects of MI on self-care confidence and on proxy measurement of specific self-care behaviors, such as physical activity and functioning, did not last over 3 months if administered only one time [32]. Similar results emerged from a recent meta-analysis [33].

Thus far, it is still unclear if administrating face-to-face MI more than once over 1 year might stabilize the positive effects of MI on self-care behaviors in patients with HF, and additional evidence is required to determine whether performing a MI on the dyad (patients and caregivers) is better than applying MI only to the individual patient [33]. For these reasons, this study protocol designed a prospective, parallel-arm, open-label, 3-arm, controlled trial for purposing the following aims: (1) to test the efficacy of a structured program including scheduled MI interventions in improving self-care behaviors (specifically, self-care maintenance) among patients with HF at 3 months from the enrollment; (2) to test the effect of a structured program including scheduled MI interventions on secondary outcomes (eg, self-care monitoring, QoL, sleep disturbance) at 3, 6, 9, and 12 months from the enrollment; and (3) to corroborate the superiority of the caregivers’ participation to the structured program including scheduled MI interventions over the program administrated only to individual patients in enhancing self-care behaviors.

## Methods

### Trial Design

This is a prospective, parallel-arm, open-label, 3-arm, controlled, and superiority randomized controlled trial (RCT). This protocol was designed and reported following the SPIRIT (Standard Protocol Items: Recommendations for Interventional Trials) 2013 statement: defining standard protocol items for clinical trials (see Multimedia Appendix 1).

### Sample and Setting

Outpatients referred to the heart failure clinic and inpatients at discharge after hospitalization for HF will be enrolled in the study. The single center where the study will be implemented is the IRCCS Policlinico San Donato, northern Italy. The recruitment strategy will be based on enrolling patients continuously until the predetermined sample size is achieved.

### Inclusion and Exclusion Criteria

The following inclusion criteria will be used for patients: being 18 years and older, diagnosis of HF with New York Heart Association (NYHA) Class II-IV, no acute coronary events within 3 months, consent to participate in the study, score ≤ 2 to at least 2 items of the Self-Care of Heart Failure Index 6.2 (SCHFI 6.2) at baseline [34], scores on Six Item Screener >4 [35], living at home, understanding of spoken and written Italian. The exclusion criteria for patients will be severe cognitive impairment (score 0-4 on the Six-item Screener) [35], acute coronary events that occurred within 3 months, living in nursing homes or residential settings, and caregivers unwilling to participate in the study.

The following inclusion criteria will be used for caregivers: being 18 years or older, being the primary informal caregiver identified by the patient, consent to participate in the study, and understanding of spoken and written Italian. Their unavailability will give the exclusion criterion for caregivers to participate in the study.

### Instruments and Outcomes

The measurements for patients will be based on collecting sociodemographic and clinical characteristics data (eg, age, gender, NYHA class), SCHFI 6.2 [34], Heart Failure Somatic Perception Scale to assess patient’s ability to feel the symptoms of HF [36], Six Item Screener to identify subjects with cognitive impairment [35], Kansas City Cardiomyopathy Questionnaire (KCCQ) to assess HF-specific QoL [37], Mutuality Scale (MS) to assess the feeling of intimacy and positive relationship between patient and caregiver [38], 12-Item Short Form Survey (SF-12) to measure generic health-related QoL [39], Pittsburgh Sleep Quality Index (PSQI) to assess sleep quality [40], Hospital Anxiety and Depression Scale (HADS) to detect depression and anxiety [41], Montreal Cognitive Assessment (MoCA) to detect mild cognitive impairment [42], and Charlson Comorbidity Index (CCI) to assess comorbidities [43].

The measurements for caregivers will be based on collecting sociodemographic data (eg, age, gender, marital status, and relationship with the patient), the Caregiver Contribution to Self-care of Heart Failure Index (CC-SCHFI) to measure the caregiver contribution to self-care in patients with HF [44], SF-12 [39], MS [38], Caregiver Preparedness Scale to assess how the caregiver feels prepared to care [45], HADS [41], Multidimensional Scale of Perceived Social Support to assess the level of social support perceived by patients with HF in managing the disease [46], and PSQI [40].

All the tools used to assess both patients’ and caregivers’ outcomes are constituted by validated and widely used instruments. The SCHFI 6.2 [34] is an instrument adopted to assess patients’ self-care, which is the primary outcome. It is a widely used scale that comprises 3 subdimensions: self-care maintenance, self-care management, and self-care confidence. A 0 to 100 score can be attributed to each dimension; scores higher than 70 indicate an adequate self-care level. The SCHFI 6.2 [34] will also be used to assess the self-care maintenance at 6, 9, and 12 months from enrollment. Several additional secondary outcomes will be evaluated at a patient level using the measurements described below.

The Heart Failure Somatic Perception Scale is the instrument used to measure physical HF symptoms. It is an 18-item Likert scale that assesses the extension of the discomfort due to symptoms perceived by patients in the week before assessment. The score for each item can range from 0 (*I did not have the symptom*) to 5 (*extreme discomfort*). Once scores are summed, higher values indicate higher symptoms bothersomely.

The Six Item Screener [35] is adopted to identify cognitive impairment or dementia; patients’ assessment using this tool requires a 3-item recall test, and it only takes 1 to 2 minutes to be administered: the subject should be able to repeat the 3 items initially and recall them after 5 minutes. The number of errors recorded in patients’ answers is used as a cutoff point. The KCCQ [37] assesses physical function, symptoms, social function, self-efficacy, and QoL in patients with HF. The KCCQ is a 23-item Likert scale used to measure the health status responsive to changes in clinical condition. The KCCQ scoring regarding health status can range from 0 to 100: 0-24 indicates very poor to poor; 25-49 poor to fair; 50-74: fair to good; and 75-100 good to excellent.

The MS is a 15-item Likert instrument used to measure mutuality from the patient’s or the caregiver’s perspective. Each item can range from 0 to 4. The mean of all item scores constitutes the overall scale score; higher scores indicate better mutuality. The SF-12 [39] is a practical, reliable, and valid tool adopted to measure physical and mental health status. It is a 12-item short-form health survey with eight domains and 1 or 2 items per domain: physical functioning, role-physical, bodily pain, general health, vitality, social functioning, role-emotional, and mental health. The Physical Component Summary (PCS) and Mental Component Summary (MCS) scores are composed of each health domain score. Scores range from 0 to 100; higher scores indicate better physical and mental health functioning. A score of 50 or less on the PCS-12 determines the physical condition; a score of 42 or less on the MCS-12 indicates “clinical depression.”

The PSQI [40] is a self-report questionnaire used to screen patients for the presence of significant sleep disturbance experienced in the month before the assessment. The measure consists of 19 individual items, creating 7 components that are summed to obtain a global PSQI score ranging from 0 to 21; higher scores indicate worse sleep quality. The HADS [41] is a 14-item measure used to detect anxiety and depression in patients. Items are rated on a 4-point scale. The HADS produces 2 scales, 1 for anxiety (HADS–A) and 1 for depression (HADS–D); anxiety and depression are confirmed by scores equal to or greater than 11.

The MoCA is used to detect mild cognitive dysfunction. It assesses different cognitive domains: attention and concentration, executive functions, memory, language, visuoconstructional skills, conceptual thinking, calculations, and orientation. Scores on the MoCA range from 0 to 30; a score of 26 and higher is considered normal. The CCI [43] predicts 10-year survival in patients with multiple comorbidities. The updated index of 12 comorbidities predicts in-hospital mortality; the severity of comorbidity is categorized into 3 grades: mild, moderate, and severe, with CCI scores of 1-2, 3-4, and ≥5, respectively.

The following tools have been used to evaluate the caregivers’ specific secondary outcomes. The CC-SCHFI [44] comprehends 10 items that assess the caregiver’s contribution to maintaining a stable condition and 10 items that assess the caregiver’s ability to monitor and recognize symptoms of HF decompensation, implement adequate treatments, evaluate those treatments, and help patients to take part in each phase of the self-care process. Each measure uses a 4-point Likert response scale with a score from 0 to 100; higher scores indicate a higher contribution to self-care.

The Caregiver Preparedness Scale is an instrument that consists of 8 items that ask caregivers how prepared they feel to handle multiple domains of caregiving. Responses are rated on a 5-point Likert scale with scores ranging from 0 to 4. The scale is scored by calculating the mean of all items. Higher scores indicate higher caregiver preparedness. The Multidimensional Scale of Perceived Social Support is a 12-item scale of perceived appropriateness of the support offered by family, friends, and significant other. The measure uses a 5-point Likert scale. The score can range from 12 to 84, and a higher score indicates greater social support perceived by the caregiver.

### Intervention and Participant Timeline

All patients meeting the inclusion criteria and not any exclusion criteria will be randomized by the researchers responsible for the study after having signed a consent form. Patients will be informed about the single allocation and will not be aware of the randomization list and allocation sequence. The intervention will be administered by nurses trained in HF self-care and MI.

The study flowchart is shown in Figure 1. In the first interventional arm, the MI intervention will be administered to patients only, and caregivers will receive standard education. MI is used to reinforce areas of inadequate self-care (eg, low physical activity or not having a low-salt diet) and to agree with the patients on the steps to be adopted to modify their behavior. MI focuses on a tailored patient approach to improve patients’ adherence to self-care behaviors. The intervention will last approximately 30 minutes. Thereafter, the nurse who performed the MI will contact the patients over the phone 3 times every 2 weeks from the first MI during the first 2 months after MI to strengthen the intervention. Then, the intervention will be used again after 3, 6, 9, and 12 months from enrollment. After each MI session, both patients and caregivers will be asked to complete the follow-up questionnaires post enrollment as described in the “Instrument” section. In the second interventional arm, MI intervention will be administered both to patients and caregivers. The intervention will be administered to the dyad in 1 session, and patients and their caregivers will receive the reinforcing educational treatment calibrated on the specific lacking areas of patients’ self-care behaviors. After each MI session, both patients and caregivers will be asked to complete the follow-up questionnaires post intervention. In the control group, the dyads will receive only traditional educational treatment and complete the questionnaires after 3, 6, 9, and 12 months of follow-up post intervention. Enrolled dyads will be monitored by the research team responsible for recruitment and follow-up.

**Figure 1 figure1:**
[figure not shown]
Study flowchart. MI: motivational interviewing.

### Training for Nurses

Nurses will participate in a training program to acquire the competence to conduct a MI. The education program will be provided to nurses by an expert psychologist.

### Sample Size Calculation

For determining sample size, based on a recent literature review [33], it was hypothesized that both experimental arms would show an improvement in self-care maintenance, and the adequacy of self-care maintenance scores in the experimental arm was shown in approximately 50% (n=250) of patients. Current Italian data indicated that roughly 20% (n=238) of Italian adults with HF reported adequate scores of self-care maintenance (scores higher than 70 are considered adequate) [47,48]. For this reason, the sample size estimation was based on a 2-sample proportions test: the expected proportion in experimental arms was equal to 50% of adequate scores (proportion 1) versus 20% of the adequate score in the control group based on the current descriptive literature (proportion 2, delta=30%). Setting alpha at .05 and power at 0.90, the number per group to identify significant differences was equal to 52. Therefore, as the study has 3 arms, 156 participants are required to test the differences in proportions between groups. Given the likelihood of a 15% rate of dropouts as per previous studies [32], the total sample size was equal to 180 diads (n=60 per arm). A consecutive screening and enrollment will be performed.

### End Points

The end points of this study are designed for the specific aim focused on testing the efficacy of a structured program, including scheduled MI interventions, in improving self-care maintenance. Precisely, the primary end point is the difference between self-care maintenance levels between the 2 groups in the 3-month follow-up. The secondary end points are the differences between self-care maintenance, self-care monitoring, and self-care management at 6, 9, and 12 months of follow-up after enrollment.

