### Statistical Analysis

Analyses will be performed within the framework of intention-to-treat analysis. Sociodemographic and clinical characteristics will be summarized and compared between groups in the baseline. For the primary end point, the differences between proportions of adequate self-care maintenance in the 3-month follow-up will be assessed using the chi-square test (or the Fisher exact test if adequate) and performed to compare the first experimental arm (MI delivered only to patients) and control group and between the second experimental arm (MI delivered to the dyad) and control group.

In addition, beyond the comparison between proportions aimed to detect clinically meaningful differences between groups, the standardized 0-100 scores of self-care maintenance will be compared using a 1-way ANOVA with post hoc comparisons adjusting the significance according to Bonferroni. A stepwise logistic regression model based on a dichotomic outcome (adequate self-care vs inadequate self-care scores) will be used to encompass the effects of clinical and sociodemographic covariates in determining the association between the group and the proportion of adequate self-care. The first step of the stepwise approach will include the trial group as an independent variable to determine the odds ratios, highlighting the associations between each group and the dichotomic outcome. The second step will allow authors to include the covariates that show significant linear relationships with the outcome to adjust the associations described in the first step. This model will be evaluated using goodness-of-fit tests, such as the Hosmer-Lemeshow test. The same approach will be used by considering the standardized 0-100 scores of self-care maintenance as the dependent variable and, therefore, in the framework of multiple linear regression. While the logistic regression will provide an association between the adequacy of self-care maintenance and the arm by accounting covariates for adjusting the estimate, the multiple linear regression will highlight the amount of variance explained by belonging to each arm, accounting for the same covariates used in the logistic regression.

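### The End Points section defines the primary end point as an unscaled difference between two unnamed groups, although the sample size and primary analysis use the proportion adequate in two MI-versus-control comparisons

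*Protocol article*

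**What the plan says.** All references are to the protocol article.

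- **End Points:** "the primary end point is the difference between self-care maintenance levels between the 2 groups in the 3-month follow-up". The section does not say whether *levels* means the 0-100 score or adequacy, or which two of the three arms are meant.
- **Statistical Analysis, primary test:** "For the primary end point, the differences between proportions of adequate self-care maintenance in the 3-month follow-up will be assessed using the chi-square test". Fisher's test is the stated alternative. Each MI arm is set against control, which makes two comparisons, and no adjustment is stated for the pair.
- **Statistical Analysis, score analysis:** this is brought in as an addition to the test of proportions. It says that "the standardized 0-100 scores of self-care maintenance will be compared using a 1-way ANOVA with post hoc comparisons adjusting the significance according to Bonferroni". Stepwise logistic and linear regressions follow.
- **Sample Size Calculation:** 50% adequate in the experimental arms against 20% in control. "Setting alpha at .05 and power at 0.90, the number per group to identify significant differences was equal to 52". This gives 156 in three arms, and 180 dyads (60 per arm) after a 15% dropout allowance.
- **Adequacy cut-off:** Instruments and Outcomes and Sample Size Calculation put adequacy strictly above 70. The time-to-event paragraph of Statistical Analysis counts a score of exactly 70 as adequate.

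**The concern.** The section that defines the primary end point does not match the sections that size and analyse it. It implies one contrast where the analysis has two, and it leaves the scale open where the analysis fixes a binary outcome. The same variable at the same visit is then tested in two ways with different error control: unadjusted for the proportions, Bonferroni for the scores. The stated power of 0.90 belongs to the proportions only.

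Timing makes this matter. The Results section says data collection ended in May 2021 and analysis was planned by December 2022, in a trial that is open-label for participants and interventionists. A definition that fits more than one result should be closed before results are seen. Otherwise a score result could be reported as primary on the strength of the End Points sentence.

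**Working it through.** **1. The plan's own figure.** Inputs from Sample Size Calculation: p1 = 0.50, p2 = 0.20, alpha 0.05 (two-sided, from Statistical Analysis), power 0.90. With mean proportion 0.35 and pooled variance under the null:

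n = [1.960 × √(2 × 0.35 × 0.65) + 1.2816 × √(0.25 + 0.16)]² / 0.30² = (1.322 + 0.821)² / 0.09 = 51.01, rounded up to **52**.

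This matches the stated 52 exactly, as one two-sided 5% comparison of two proportions. Three arms give 156, and 156 × 1.15 = 179.4, hence 180. If 15% of 60 drop out, 51 per arm remain.

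**2. Error from the two chi-square comparisons.** With no true effect:

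- if the comparisons were independent, 1 − 0.95² = 9.75%;
- with a shared control and equal arms (correlation 0.5), the bivariate normal calculation gives **9.1%**.

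**3. What free choice of test adds.** The documents give no score distribution, so these are assumptions: normal scores with common SD 15, 20% of control above 70, 51 per arm, and post hoc tests over three pairs (0.05/3 each). The value of the SD has no influence: fixing the share above 70 in each arm fixes the shift in SD units, and repeating the run with SD 25 gave the same results within simulation error. With no effect, over 40,000 simulated trials, the chance of at least one significant MI-versus-control result is:

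| Rule | Probability |
|---|---|
| Chi-square, unadjusted | about 9.0% |
| Score, Bonferroni | about 3.2% |
| Either counts | about 10.6% |

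Repeated runs gave 8.9-9.0% for the chi-square and 10.4-10.6% for either, so free choice adds about **1.5 points**.

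**4. How often the two tests disagree on one comparison** (same assumptions):

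| True share adequate in MI arm | Opposite conclusions |
|---|---|
| 35% | about 23% |
| 40% | about 22% |
| 50% (planned) | about 8% |

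**5. Power if alpha is split over the two comparisons.** At two-sided 0.025 the critical value is 2.2414. Power = Φ[(0.30√n − 2.2414 × 0.6745) / 0.6403]:

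- n = 51: Φ(0.985) = 83.8%
- n = 52: Φ(1.017) = 84.6%
- n = 60 (no dropout): Φ(1.268) = 89.8%

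Keeping 90% power at 0.025 would need (1.512 + 0.821)² / 0.09 = 60.5, so 61 evaluable per arm.

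**The case against.** The strongest reply is that the protocol already ranks the tests. Statistical Analysis attaches the chi-square test of proportions to the primary end point by name and brings in the ANOVA only as an addition. The sample size rests on proportions. Instruments and Outcomes uses the word *level* for adequacy, and a contrast of two groups fits a pairwise chi-square better than a one-way ANOVA over three arms. All of this stands. A reader might infer that the End Points wording makes the ANOVA the primary test, or that the two tests have equal standing. The documents do not support that, because the sentence names no test and the other sections favour the binary one.

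A reader might also see a third definition in Instruments and Outcomes, which refers to "self-care, which is the primary outcome" and lists three dimensions. That is loose wording. The Objective, the aims in the Introduction, Sample Size Calculation, End Points and Statistical Analysis all name self-care maintenance. The same Instruments section says the index will also assess maintenance at 6, 9 and 12 months, which implies that maintenance at 3 months is primary.

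A further fair point is that most of the excess error in step 3 is ordinary multiplicity, and that a binary test at 0.05 and a score test at 0.05/3 will sometimes disagree even under a perfect definition. That limits what the figures show. It does not repair the definition: the End Points sentence still describes one contrast on an unnamed scale, and the other sections describe two contrasts on a binary scale.

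**Conclusion.** The point holds as a faulty definition. The End Points sentence is imprecise on scale and on groups, and it conflicts with the two-comparison binary analysis that the rest of the protocol supports. It permits, but does not require, the score analysis to be presented as primary.

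The practical exposure is at moderate benefit, where the choice of test would change the conclusion in roughly one comparison in four or five. At the planned effect it is about one in twelve. These figures rest on normal scores, a common SD, 51 per arm and three post hoc pairs, none of which except the 51 can be derived from the documents. Inflation of error from choosing between tests is small. The larger part, about 9% against a nominal 5%, comes from the two unadjusted chi-square comparisons, and rewording the end point alone would leave it in place. It should be corrected before analysis, and the correction is cheap.

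**What to change.** Before analysis:

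1. Replace the End Points sentence with wording such as: *The primary end point is the proportion of patients with adequate SCHFI 6.2 self-care maintenance at 3 months from enrollment, compared between each MI arm and control (two comparisons).*
2. Use one adequacy cut-off throughout, either strictly above 70 or 70 and above.
3. State the error control for the two comparisons (an alpha split or a fixed testing order). If alpha is split, restate the power: about 84-85% per comparison at 0.025 with 51-52 per arm.
4. Label the score ANOVA and the regressions as supportive.
5. As a minor edit, write self-care maintenance where Instruments and Outcomes names the primary outcome.

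The cost is a few sentences and no new analysis. A significant score result could no longer be presented as primary, and the stated power falls from 90% if alpha is split. A fixed testing order would keep each test at 0.05, but the second comparison could be claimed only if the first succeeds.
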